#### Intervention Adaptation

Participants will be recruited through the Swiss CASCADE cohort and through flyers posted in the affiliated Korean institutions and clinics. After obtaining consent, focus groups or individual interviews will be organized at an easily accessible site and in participants’ language. Focus groups will be coded by 2 members of the team in each country and linguistic region and will be audiotaped with participants’ explicit consent. Participants will be asked to *think aloud* while viewing electronic mockups of the intervention and while navigating a final version of the digital health intervention. The latter sessions will be videotaped.

Clinicians involved in genetic consultations will be identified through the CASCADE Consortium in Switzerland; through the Schweizerischen Arbeitsgemeinschaft für Klinische Krebsforschung, Network for Cancer Predisposition Testing and Counseling in Switzerland; and through the KOHBRA network in Korea. They will be recruited via email and/or invitation letters and will also provide consent. Semistructured exploratory questions will elicit their opinions on structural barriers to HBOC cascade genetic testing. At a later stage, they will also view a nearly final version of the digital health intervention and will provide feedback. Sessions will be audiotaped and videotaped with clinicians’ consent.

#### Intervention Efficacy

After they complete the baseline questionnaires (T_1_), probands (index case) in both countries who agree to participate in an RCT and test the effects of the adapted Family Gene Toolkit will be emailed a unique URL link and passcode allowing them access to the digital health intervention. Furthermore, they will be able to log in and review the intervention modules multiple times using the same URL link and passcode. The system will randomize participants in a 1:1 ratio to either the digital health intervention or the comparison website. Stratification by country (Switzerland vs Korea) will be facilitated with different URL links for participants from each country. Participants will receive weekly email or text alerts, encouraging them to visit the website and complete viewing of the contents of the digital health intervention within 4 weeks. They will also receive email or text alerts to complete a knowledge quiz, an exercise for value clarification related to genetic testing, and a family communication rubric that will be included in the content of the different modules. Participants randomized to the comparison website will receive 1 email alert 2 weeks after they engage with the website. Relatives will be allocated to the same study arm as the respective proband and will also receive a URL link and a unique passcode. Relatives will first be asked to complete a consent form and then to complete the baseline survey, after which they will have access to either the adapted Family Gene Toolkit or the comparison.

Primary and secondary outcomes will be assessed at 2 months (T_2_) and 6 months (T_3_) after the intervention. We selected the 2- and 6-month follow-up time points to measure the short-term and long-term intervention effects, in line with our previous studies [33,50]. To minimize the attrition rate, if a response has not been received within 2 weeks from the time participants receive the URL link to the follow-up survey, then the study personnel will make 3 attempts to contact them by email or phone and encourage them to complete the survey.

### Measures and Outcomes

#### K-CASCADE

The core questions of the Swiss CASCADE cohort [14] constitute the basic measurements for the K-CASCADE. Instruments are purchased (if not available for free) and will be translated into Korean (if not available) following the World Health Organization’s translation guidelines. The baseline survey covers cancer diagnoses and surveillance, use of and experience with genetic testing (for testers and nontesters), communication with health care providers, and satisfaction with cancer genetic services. It assesses information about prophylactic surgeries; epidemiological data about personal, reproductive, and family history of breast and ovarian cancer; and modifiable lifestyle risk factors (smoking, drinking, physical activity, etc). The baseline survey also assesses demographic characteristics and psychosocial variables, for example, the fear of cancer recurrence and self-efficacy to use services, which constitute the basis for creating the tailored messages provided by the adapted Family Gene Toolkit. These instruments are listed in Table 1. The Korean survey will be pilot tested with 10 study participants for comprehension and accuracy.

**Table 1 table1:** Demographics and psychosocial characteristics.

Variables			Instruments		Cronbach α		Test-retest reliability		Assessment		
									Baseline		Follow-up
Demographics, personal, and family cancer history			Self-report [55]		—^a^		—		✓^b^		
**Tailoring variables**											
	Degree of relationship between proband-relatives (eg, first degree)	Self-report		N/A^c^		N/A		✓			
	Fear of cancer recurrence (for patients)	Concerns About Recurrence Scale [56], 4 items, 7-point Likert scale		.93		0.91		✓			
	Self-efficacy dealing with cancer (for patients)	Self-efficacy–HBOC^d^-related cancer [57], 14 items, 7-point Likert scale		.80		0.71		✓			
	Self-efficacy using genetic services	1 item, 7-point Likert scale		N/A		N/A		✓			
	Family support	Family Support in Illness [58], 10 items, 7-point Likert scale		.86		0.83		✓			
	Family hardiness	Family Hardness Index [59], 20 items, 7-point Likert scale		.90		0.82		✓			
	Satisfaction with genetic counseling (for tested individuals)	Multidimensional Impact of Cancer Risk Assessment [60], 19 items, 7-point Likert scale		.81		—		✓			
	Barriers and facilitators for genetic services	Barriers and facilitators for genetic services [61], 11 items, multiple choice		N/A		N/A		✓			

^a^Not available.

^b^The variable will be assessed at the specific time frame.

^c^N/A: not applicable.

^d^HBOC: hereditary breast and ovarian cancer.

#### Intervention Adaptation

A trained moderator will ask focus group participants to answer semistructured exploratory questions designed to elicit their opinions on the most pressing issues for family communication, using appropriate probe questions to explore potential cultural interpretations. The interview guide explores issues around family communication that took place during the genetic consultation, decision making related to the disclosure of test results to relatives, and attitudes toward using digital health platforms. Participants will also rate their satisfaction with the content, format, and appearance of the website. Assessing intervention feasibility also involves assessing the number of modules accessed, time spent on each module, and the utilization of links, which are automatically recorded on the website.

#### Intervention Efficacy

Data to evaluate the magnitude of intervention effects will be assessed using the instruments listed in Table 2. These have strong psychometric properties and have been used in previous studies on patients with cancer. Most of these instruments have been translated into and validated in German, French, and Italian and will be translated into and validated in Korean. Primary and secondary outcomes are assessed at the 2-month and 6-month follow-up surveys. Satisfaction with the intervention and acceptability will be assessed at the 2-month follow-up with questions about intervention usefulness, ease of use, clarity, appropriate length, level of detail, relevance, and interest with a 7-item survey (Likert scale ranging from 1=low to 7=high) [62,63].

**Table 2 table2:** Instruments to assess primary and secondary outcomes.

Concepts			Instruments		Cronbach α		Test-retest reliability		Assessment		
									Baseline		Follow-up
**Primary outcomes**											
	Proportion of informed relatives	Website data		N/A^a^		N/A		✓^b^		✓	
	Intention to inform relatives	Informing Relatives Inventory [64], 68 items, 7-point Likert scale		.86		—^c^		✓		✓	
	Intention for genetic testing (untested relatives)	1 item, 7-point Likert scale		N/A		N/A		✓		✓	

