### Objectives

The DIALOGUE study will build a bilateral research infrastructure to support collaboration and multidisciplinary initiatives around HBOC in Switzerland and Korea. The specific aims are to develop the K-CASCADE (Korean–Cancer Predisposition Cascade Genetic Testing) cohort in Korea by expanding an existing research infrastructure developed by the CASCADE Consortium in Switzerland; develop a digital health intervention to support open communication and cascade genetic testing in HBOC families, based on the linguistic and cultural adaptation of the Family Gene Toolkit; evaluate the efficacy of the digital health intervention on primary (communication of genetic test results to relatives and cascade genetic testing) and secondary (psychological distress, genetic literacy, coping, and decision making) outcomes; and explore the translatability of the platform using the reach, effectiveness, adoption, implementation, and maintenance (RE-AIM) framework.

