#### Aim 2: Adapt the Digital Health Intervention

The content of the Family Gene Toolkit is driven by theory [36] and supported by empirical findings [37-41]. It is designed to address challenges related to the quantity and complexity of genetic information mutation carriers are asked to communicate with family members [42,43]. Understanding HBOC (eg, probability of mutation, prognosis, prevention, and treatment) and the accuracy of genetic testing are important for decision making. Inherited cancer risk requires ongoing management and, thus, active coping with health challenges. Mutation carriers’ personal values and communication skills are important for the disclosure of genetic cancer risk. The Family Gene Toolkit embraced the above challenges and included 4 modules designed to increase knowledge of cancer genetics (module 1), provide decisional support for genetic testing to untested relatives (module 2), increase active coping with common challenges faced by HBOC families (module 3), and provide skills-building communication training (module 4; Figure 1). The adapted Family Gene Toolkit will include the 4 original modules and a fifth module about the management of cancer risk based on recommendations from the National Comprehensive Cancer Network [44].

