**Secondary outcomes**											
	Psychological distress	Profile of Mood States [65], 37 items, 7-point Likert scale		.86		—		✓		✓	
	Genetic literacy—genetic affinity	Risk Factor Knowledge Index [39], 17 items, true, false, and do not know		.89		0.85		✓		✓	
	Genetic literacy—cancer genetics	Breast Cancer Genetics Index [66], 12 items, true, false, and do not know		.82		0.81		✓		✓	
	Coping with stressful events	Brief Cope [67], 25 items, 7-point Likert scale		.81		0.78		✓		✓	
	Decision making—untested individuals	Decisional Conflict Scale-HBOC^d^ Genetic Testing [68], 16 items, 7-point Likert scale		.96		—		✓		✓	
	Decision making—tested individuals	Decisional Regret-Genetic Testing [69], 5 items, 7-point Likert scale		.87		—		✓		✓	

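### Cascade genetic testing is named as a primary outcome, but Table 2 measures only intention to test among untested relatives, a group the intervention itself may deplete

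*Protocol article*

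**What the plan says.** The Objectives section lists the trial's outcomes as "primary (communication of genetic test results to relatives and cascade genetic testing"), followed by the secondary outcomes. The Abstract says the same. The Background section describes cascade screening as identifying relatives and testing them, so the natural reading of the objective is completed testing.

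Table 2 has three primary rows: the proportion of informed relatives, intention to inform relatives, and "Intention for genetic testing (untested relatives"). The last is measured by "1 item, 7-point Likert scale" and is ticked at both baseline and follow-up. On timing, the Intervention Efficacy section under Measures and Outcomes says "Primary and secondary outcomes are assessed at the 2-month and 6-month follow-up surveys".

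Among the secondary outcomes, two instruments are split by testing status. "Decision making—untested individuals" is measured by a decisional conflict scale and "Decision making—tested individuals" by a decisional regret scale. Both are ticked at baseline and follow-up.

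Testing itself appears in the baseline survey, which covers "use of and experience with genetic testing (for testers and nontesters"), and again in the analysis section as an example of a descriptor to tabulate. The analysis section assigns the Wilcoxon-Mann-Whitney test to the proportion of informed relatives. The remaining primary outcomes and the secondary outcomes are to be described. The article gives no rule for a relative who is tested after baseline.

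**The concern.** There are two linked problems.

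First, the objective and the measure differ. An intention score is not uptake, and no outcome row captures uptake at 2 or 6 months. A reader of the results would take the intention comparison as the trial's answer on cascade testing.

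Second, the group in which intention is measured may depend on treatment. One component of the intervention is meant to "provide decisional support for genetic testing to untested relatives (module 2"). A relative who decides in favour and is tested within six months has no intention left to report. If such relatives leave the set, what remains is those who did not act. The arm that prompts more testing then loses more of its willing relatives. The comparison is no longer between randomised groups, and the selection works against an intervention that succeeds.

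The same movement affects the decision scales. A relative tested between surveys passes from the conflict scale to the regret scale and has no baseline-to-follow-up comparison on either.

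**Working it through.** **Objective against measure.** This step needs no assumption. The Objectives and the Abstract name cascade genetic testing as primary. Of the Table 2 rows, one primary row concerns testing (intention). Two secondary rows are decision scales assigned by testing status. None records whether a relative was tested.

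**Is untested status updated?** Table 2 does not say. Two features point to status at each survey: an intention item does not apply to someone already tested, and both status-specific decision scales are ticked at follow-up. This is an inference, and the arithmetic below depends on it.

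**The plan's own figures.** The article gives none for intention or uptake. Its sample size of 104 evaluable probands rests on a 25% increase in informed relatives, so there is nothing to reproduce for this outcome. Every input below is an assumption.

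**Hand example.** Take 100 relatives per arm, all untested at baseline. Their intention before any of them acts sits at scores 2, 4 and 6.

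- Control, 20/40/40: mean (40 + 160 + 240)/100 = 4.40.
- Intervention, 15/40/45: mean (30 + 160 + 270)/100 = 4.60. The true gain is +0.20.

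Suppose all who get tested come from score 6, with 10 tested in the control arm. The control relatives still untested have mean (40 + 160 + 180)/90 = 4.22.

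| Tested, intervention arm | Mean of those still untested | Difference from control |
|---|---|---|
| 10 | (30 + 160 + 210)/90 = 4.44 | +0.22 |
| 20 | (30 + 160 + 150)/80 = 4.25 | +0.03 |
| 30 | (30 + 160 + 90)/70 = 4.00 | -0.22 |

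In the last row uptake has tripled and the reported difference is negative. If all 100 are kept and tested relatives are scored 7, that row gives (380 + 70)/100 = 4.50 against (280 + 210)/100 = 4.90, or +0.40.

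**Less extreme selection.** Intention is simulated as normal with control mean 4.5 and SD 1.5, rounded and limited to 1 to 7. The log-odds of being tested rise by a slope of 0, 1 or 2 per point of intention. With a true gain of about +0.28, the difference among those still untested is:

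| Uptake, control vs intervention | Slope 0 | Slope 1 | Slope 2 | All kept, tested scored 7 (slope 1) |
|---|---|---|---|---|
| 10% vs 10% | +0.28 | +0.29 | +0.29 | +0.26 |
| 10% vs 20% | +0.27 | +0.14 | +0.10 | +0.38 |
| 10% vs 30% | +0.28 | -0.01 | -0.09 | +0.53 |
| 10% vs 40% | +0.28 | -0.16 | -0.28 | +0.71 |

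A larger true gain of about +0.46 resists better. At 10% versus 40% it falls to +0.04 (slope 1) or -0.08 (slope 2). With no gain in intention but uptake of 10% versus 30%, the difference is -0.30 (slope 1) or -0.39 (slope 2).

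Distortion therefore needs both conditions: unequal uptake, and testing concentrated among the more willing. With either absent, the difference is essentially correct.

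**The case against.** The strongest reply is that the selection mechanism is inferred. Untested relatives could mean untested at baseline and followed whatever they do next, and a rule for those tested in between could sit in the statistical analysis plan, which is not shown. This stands. A reader might infer that every relative who gets tested is certain to drop out, but the article does not say so. What survives is that no Table 2 outcome measures completed testing, and that relatives untested at baseline would still need a defined value once tested.

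A second reply is that assigning decision scales by current status would require the follow-up survey to establish that status, so uptake might be derivable. The analysis section also lists genetic testing as a descriptor without limiting it to baseline. This too is fair. A reader might conclude that the trial cannot answer its question on cascade testing, and the documents do not support going that far. They show that uptake is not a named outcome, not that the data will be absent.

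Third, the consequence is limited. Intention is only described, and the one formal test and the sample size concern informed relatives. This stands in full.

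Fourth, the reversals come from chosen inputs, and smaller uptake differences shrink the effect without reversing it. Scoring a tested relative as the best result is also a value choice, since the toolkit aims at informed decisions. Both points are right. They are why completed testing is better reported directly, with any composite kept as a sensitivity summary.

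**Conclusion.** The point holds in two parts of different strength. The mismatch is on the page: cascade testing is declared primary, and only intention is measured for it. The bias is conditional. It arises if untested status is applied at each survey, if uptake differs between arms, and if the more willing test first. A working intervention would tend to produce the second condition, and using intention as a stand-in for testing presupposes the third.

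Under those conditions, with a true gain of 0.28 points, the reported difference is roughly halved or worse at 10% versus 20% uptake (+0.14 or +0.10). It is near zero or slightly negative at 10% versus 30%, and clearly negative at 10% versus 40%. These uptake values are illustrations, not forecasts.

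It would be wrong to infer that the main efficacy test is compromised. The Wilcoxon comparison of informed relatives and its sample size do not depend on this item. The harm is a potentially misleading descriptive summary of a declared primary outcome. An analysis plan can repair it only if testing status is collected at 2 and 6 months, so it should be settled before those surveys are fielded.

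**What to change.** - Define the analysis set for the cascade-testing outcome as relatives untested at baseline (T1).
- Repeat the existing baseline testing-use item at 2 months (T2) and 6 months (T3), and add completed testing by 6 months, reported by arm, to Table 2 as the cascade-testing outcome.
- Report intention among those still untested only as supportive, always next to uptake by arm. Optionally add a composite over all relatives untested at T1, with tested relatives in the top category, as a sensitivity summary.
- Present the decision scales by testing status at T1.
- If completed testing will not be collected, restate the objective in the Abstract and the Objectives section as intention to test.

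The cost is one repeated survey item, a few lines of protocol and analysis-plan text, and a little more analysis. The sample size and the main test do not change.

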**Secondary outcomes**											
	Psychological distress	Profile of Mood States [65], 37 items, 7-point Likert scale		.86		—		✓		✓	
	Genetic literacy—genetic affinity	Risk Factor Knowledge Index [39], 17 items, true, false, and do not know		.89		0.85		✓		✓	
	Genetic literacy—cancer genetics	Breast Cancer Genetics Index [66], 12 items, true, false, and do not know		.82		0.81		✓		✓	
	Coping with stressful events	Brief Cope [67], 25 items, 7-point Likert scale		.81		0.78		✓		✓	
	Decision making—untested individuals	Decisional Conflict Scale-HBOC^d^ Genetic Testing [68], 16 items, 7-point Likert scale		.96		—		✓		✓	
	Decision making—tested individuals	Decisional Regret-Genetic Testing [69], 5 items, 7-point Likert scale		.87		—		✓		✓	
**Intervention evaluation**											
	Acceptability, detail, usefulness, relevance, and satisfaction	Intervention Evaluation [62,70], 16 items, 7-point Likert scale		—		—				✓	

^a^N/A: not applicable.

^b^The variable will be assessed at the specific time frame.

^c^Not available.

^d^HBOC: hereditary breast and ovarian cancer.

#### Intervention Translatability

Textbox 2 outlines RE-AIM outcomes to be assessed, which will help in evaluating the potential for a broader implementation and dissemination of the digital health intervention.

Reach, effectiveness, adoption, implementation, and maintenance outcomes assessed in the study.Reach (individual)Response rate of mutation carriers and relativesNumber of probands and relatives accessing the websiteDemographic, linguistic characteristics, and regionResponse rate to K-CASCADE (Korean–Cancer Predisposition Cascade Genetic Testing)Effectiveness (individual)Assess the number of times participants accessed each moduleAssess the number of relative invites initiated through the websiteEvaluate the acceptability, interest, usefulness, level of detail, relevance, and satisfaction follow-up surveyAdoption (setting, staff, and organization)Number of clinicians and new settings willing to participate in the studyDiversity (geographic, linguistic, etc) in participating settingsImplementation (setting, staff, and organization)Monitor referrals of mutation carriers from different clinical sitesEvaluate the cost for adapting modules for other hereditary cancer syndromes (eg, Lynch syndrome)Maintenance (individual and setting)Assess resources needed to maintain the websiteAssess the number of visits per month per year

### Data Management and Data Analyses

#### K-CASCADE Cohort

Korean participants’ data entered in the Swiss CASCADE platform will be available for descriptive and comparative analyses, using epidemiological and psychosocial data along with coded and nonidentified clinical data. Existing clinical data from Severance Hospital, stored in the Clinical Research Analysis Portal, will also be accessed for participants who provide additional consent. At year 4, the accrued data from Korean women will be used in conjunction with clinical data for comparative analyses with the Swiss CASCADE cohort.

#### Intervention Adaptation

The mini focus groups or interviews with HBOC families and clinicians will be audiorecorded with participants’ consent and transcribed verbatim, using codes to protect individual identification. Transcripts will be reviewed by the research team, and content will be analyzed using an iterative process of reading transcripts, coding, and comparing the data to identify salient themes. Two members of the research team in each country will also review the videotapes obtained from usability testing and the *think aloud* protocol. They will confirm that there are no functional errors on the website, color schemes and graphical images are well received, participants can navigate through various sections of the website with ease, the layout accurately conveys information, and the program works as expected. Data regarding acceptability will be analyzed using descriptive statistics.

